### **4.3.3 Data Management and Record Keeping**

The data obtained in this study will not be used for other research purposes without the consent of the patients. Strict anonymization of the collected data will be enforced, and the data will be stored on password-protected personal computers in the Department of Cardiology and the Sports Medicine Center (secured with locks).

While the possibility of personal information leakage is very low, it cannot be entirely ruled out. To protect personal information, the data analyzed will be in a de-identified form, with proper

management of the correspondence table. Additionally, meticulous care will be taken in data management to prevent any data leakage.

#### **4.4 Bias**

Adaptive randomization method will be applied to reduce intervention bias. Due to the nature of the intervention, blinding is not feasible, and thus the trial will be conducted with an open-label design.

#### **4.5 Study Participants Compliance**

Not applicable.

#### **4.6 Enrollment and Registration of Study Participants**

- (1) Confirm that candidate patients meet all inclusion criteria and do not meet any exclusion criteria.
- (2) Provide an explanation of the study and obtain consent electronically.
- (3) Assign an anonymized ID to subjects who have given consent. Randomly determine whether the subject will respond to ePRO or not on a computer before starting the study.

#### **4.7 Study Period**

From the date of study approval to March 31, 2024.

#### **4.8 Study Interruption or Termination**

The investigator shall consider whether to continue the study based on the study protocol in the following cases:

- (1) If changes to the study protocol are necessary, and the implementing medical institution cannot accommodate these changes.
- (2) If the head of the implementing medical institution issues a directive to modify the study based on the opinion of the ethics committee, and the investigator does not agree to this directive.
- (3) If the ethics committee states that the study should not continue, and the head of the implementing medical institution orders the study to be terminated.
- (4) When the principal investigator changes due to transfer or other reasons, and the study is

paused until a new principal investigator can take over the study.

## **5. Criteria for Inclusion, Exclusion, and Discontinuation**

### **5.1 Inclusion Criteria**

Adult cardiovascular disease patients aged 18 and older who are currently receiving outpatient treatment. For angina and myocardial infarction, patients who have previously undergone catheter examinations; for heart failure, patients who meet the Framingham criteria and have a BNP level exceeding 100 pg/ml at the time of case registration; for atrial fibrillation, patients diagnosed with atrial fibrillation on a 12-lead electrocardiogram.

### **5.2 Exclusion Criteria**

Individuals deemed unsuitable as subjects for this study by the principal or co-investigators. Individuals who are unable to operate electronic devices such as tablets.

### **5.3 Discontinuation Criteria**

The principal investigator or sub-investigators will discontinue the study for a subject if any of the following conditions are identified after subject registration:

- (1) An adverse event occurs, and the principal investigator or sub-investigators determine that the study should be discontinued.
- (2) The subject requests to withdraw from the study.
- (3) It is determined that the subject is inappropriate for inclusion in the study.
- (4) It becomes evident that the necessary observations and tests cannot be conducted due to the subject's circumstances.
- (5) Any other reason where the principal investigator or sub-investigators judge that the collection of questionnaire data should be discontinued.

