### **Reasons for Settings:**

- (1) was established to ensure safety considerations.
- (2) and (3) was set as part of the informed consent process, acknowledging the subjects' rights.
- (4) was established because subjects who cannot undergo necessary observations should be withdrawn from the study promptly.
- (5) was set in consideration of any other situations requiring the discretion of the principal

investigator or sub-investigators to discontinue the study.

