##### **4.1. Full Analysis Set (FAS)**

The FAS will include all subjects enrolled in this study. However, data from subjects with significant protocol violations (e.g., lack of consent, enrollment outside the contract period, or absence of efficacy data) will be excluded.

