##### **4.3. Handling of Subjects**

The Principal Investigator will make decisions regarding the handling of enrolled subjects. If any issues arise concerning subject handling, the matter will be resolved through consultation with the Lead Statistician.

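### Judgement-based discontinuation by unblinded investigators can take a randomised patient out of the primary analysis, because no visit-5 outcome is then required and the FAS drops patients without efficacy data

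*Combined protocol and SAP*

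**What the plan says.** **Stopping a subject.** Protocol 4.6 has eligibility confirmed before consent and allocation. Protocol 5.3 then provides that the principal investigator or sub-investigators "will discontinue the study for a subject if any of the following conditions are identified after subject registration". Criterion (3) reads "It is determined that the subject is inappropriate for inclusion in the study". Criterion (5) is a catch-all that leaves the stopping of questionnaire collection to their judgement. The nearest eligibility rule, in protocol 5.2, is also opinion: "Individuals deemed unsuitable as subjects for this study by the principal or co-investigators". Protocol 4.4 states that "the trial will be conducted with an open-label design".

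**Analysis set.** SAP 4 makes the FAS the main analysis and calls the approach intention-to-treat. SAP 4.1 starts from all enrolled subjects and then makes an exception: "However, data from subjects with significant protocol violations (e.g., lack of consent", followed by two further examples, enrolment outside the contract period and having no efficacy data. SAP 4.2 forms the PPS by taking violators of the inclusion and exclusion criteria out of the FAS.

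**Who decides.** SAP 4.3: "The Principal Investigator will make decisions regarding the handling of enrolled subjects". The Lead Statistician is consulted if issues arise. SAP 8.3 says that the analysis follows the setting of Subject Handling Criteria and a data review. It does not say when the criteria are set, or whether arm and outcome are hidden.

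**Primary analysis.** SAP 6.1 compares the mean change in satisfaction from baseline to final follow-up by unpaired t-test. SAP 2.7 runs that test on complete data without imputation. Under protocol 4.2 the follow-up outcome questionnaire is given at the fifth visit.

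**The concern.** Randomisation protects the comparison only for patients who are kept in the arm they were allocated to. Here an investigator who knows the arm and has seen the patient's course can end participation on opinion. If that happens before visit 5, the patient has no final score and is not counted. If such judgements are related both to arm and to how satisfied the patient would have been, the two groups in the t-test are no longer the groups that were randomised. With 25 per arm, one or two patients carry noticeable weight. There is no data monitoring committee (SAP 2.2) and no monitoring or auditing (protocol 11), so no independent party would review these decisions.

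The FAS rule adds a second, weaker worry. Its exclusions are given only as examples, and the person who decides subject handling is not blinded.

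**Working it through.** The plan gives no effect size, SD, dropout rate or power calculation, so there is no derived figure to reproduce. The only figure is the sample size: 25 × 2 = 50, which is consistent.

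**Step 1: trace the main route.**
1. Protocol 5.3(3) or (5): an investigator stops the subject before visit 5.
2. No passage asks for the visit-5 questionnaire afterwards.
3. SAP 6.1: without a final score there is no change score.
4. SAP 2.7: the t-test uses complete data only.
5. SAP 4.1: lack of efficacy data also removes the patient from the FAS, so the main analysis set no longer shows the loss.

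Each step follows from the text. The result does not fit the intention-to-treat description in SAP 4.

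**Step 2: test the second route, removal of a patient who has a score.** SAP 4.1 names three examples, none of which is an eligibility opinion. SAP 4.2 removes eligibility violators from the FAS to form the PPS, which implies that they were in the FAS. This route therefore rests only on the open-ended list in SAP 4.1 together with the discretion in SAP 4.3. It is possible, but weaker.

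**Step 3: timing.** Protocol 5.3 counts from registration, and protocol 12.1 places registration of basic details before consent. Part of the window may precede allocation, but nothing confines criteria (3) and (5) to that part.

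**Step 4: scale, as an illustration.** Inputs from the documents: 25 per arm, unpaired t-test, two-sided 5%. Assumptions: normal change scores with SD 1, no true effect, removals in the ePRO arm only, and the number removed and its link to outcome as stated.

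- Standard error of the difference with nobody removed: √(2/25) = 0.283 SD.
- The expected lowest and second-lowest of 25 standard normal values are −1.965 and −1.524.
- Removing the lowest one shifts the arm mean by 1.965/24 = 0.082 SD. Removing the lowest two shifts it by (1.965 + 1.524)/23 = 0.152 SD.
- If the judgement correlates ρ with the outcome, the shift is multiplied by ρ. At ρ = 0.5 it is 0.041 SD for one removal and 0.076 SD for two.

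Type I error, from simulations of 100,000 trials per scenario:

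| Removed from ePRO arm | Shift (SD) | Two-sided type I error |
|---|---|---|
| None | 0 | 4.9% |
| 1 to 3, unrelated to outcome | 0 | about 5% |
| 1, correlation 0.5 | 0.04 | about 5.4% |
| 2, correlation 0.5 | 0.08 | about 5.9% to 6.0% |
| 2 worst final scores | 0.15 | about 9.3% to 9.5% |

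The ranges are differences between simulation runs. Because the shift goes one way, significant results in favour of ePRO rise faster than the two-sided rate: from 2.5% with no removal to 4.6% for two removals at correlation 0.5.

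**The case against.** The strongest case against has four parts.

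- **Protocol 5.3 governs participation, not analysis sets.** This stands. A reader might infer that a patient with complete data can simply be struck out by a late eligibility opinion. SAP 4.2 points the other way, as step 2 shows. The well-supported route is through the missing visit-5 score, so the point is closely tied to the handling of missing outcomes.
- **The direction is not shown.** This stands. A reader might infer that removals must favour ePRO, because tablet difficulty could surface only in that arm. The criteria apply to both arms. Patients who cannot operate tablets are excluded at entry (protocol 5.2), and the outcome questionnaires in both arms are also collected on electronic devices (protocol 4.3.2). ePRO patients do use the tablet at every visit, so exposure is unequal, but that does not establish a direction.
- **The larger figure needs an extreme assumption.** This stands. A type I error above 9% requires the investigator to pick the two worst final scores, which do not exist yet when a patient is stopped before visit 5.
- **There are safeguards.** They are partial. SAP 2.9 delays analysis until cases and data are locked, SAP 4.3 brings in the Lead Statistician when issues arise, and SAP 5.1 tabulates eligibility violations, discontinuations and dropouts. None of these hides arm or outcome from the decision, and SAP 5.1 does not say that the counts are given by arm.

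The stated reason for criterion (3), consent and subjects' rights, fits poorly with an investigator's judgement. That is a flaw of wording and no evidence of bias. Pilot status lowers the stakes, but the SAP still tests the primary endpoint at two-sided 5%.

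**Conclusion.** The concern holds for the route through early stopping. The plan lets unblinded investigators end participation on judgement, does not ask for the outcome afterwards, and then drops the patient from the main analysis despite its intention-to-treat label. The open-ended FAS list with unblinded handling is a secondary weakness.

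Bias would arise only if stopping is related to arm and outcome. The documents allow this but do not show that it occurred, and they do not fix its direction or size. Under the assumptions above, a plausible scale is 0.04 to 0.08 SD, or 0.041/0.283 = 0.14 to 0.076/0.283 = 0.27 standard errors. The worst case of 0.15 SD is 0.152/0.283 = 0.54 standard errors. The number of removals and the correlation are assumptions.

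A reader might infer that the main result would be unusable without the change. The figures do not support that for a 50-patient pilot. Severity is moderate: a cheap correction worth making.

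**What to change.** - **Protocol 5.3:** leave the discontinuation criteria to the investigators. Add that patients discontinued under any criterion, expressly including (3) and (5), are still asked for the visit-5 outcome questionnaire unless they withdraw consent, and stay in the FAS in their randomised arm. Criterion (5) needs express mention because it is worded as stopping questionnaire collection.
- **SAP 4.1:** replace the examples with a closed list of facts fixed before randomisation: no valid consent, or enrolled outside the contract period. State that eligibility violators remain in the FAS and are removed only from the PPS.
- **SAP 4.3 and 8.3:** fix the Subject Handling Criteria before outcome data are reviewed. Decide cases together with the Lead Statistician on a listing without arm or outcome.
- **SAP 5.1:** report discontinuations and exclusions by arm, with reasons.

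**Cost:** a few sentences, one listing, and one further questionnaire request per discontinued patient. A few ineligible patients will stay in the main analysis, which the PPS addresses. Patients who withdraw consent or do not answer will still have no score and will still drop out of the t-test under SAP 2.7. The change does not remove that loss, but the report by arm makes it visible.

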### **Reasons for Settings:**

- (1) was established to ensure safety considerations.
- (2) and (3) was set as part of the informed consent process, acknowledging the subjects' rights.
- (4) was established because subjects who cannot undergo necessary observations should be withdrawn from the study promptly.
- (5) was set in consideration of any other situations requiring the discretion of the principal

investigator or sub-investigators to discontinue the study.

## **6. Study Treatment**

### **6.1 Contents of the Study Treatment**

The system used to collect ePRO questionnaires in this clinical trial is as follows:

Name: Smart-Pro (tentative name)

System Provider: Chubu Electric Power Co., Inc.

Usage Purposes:

Collection, accumulation, and utilization of ePRO (AFEQT, KCCQ, SAQ) data

Tool for obtaining electronic informed consent.

Random allocation tool for assigning patients to either the ePRO group or the control group (ePRO non-response group).

### **6.2 Concomitant Therapy**

Standard treatment for atrial fibrillation, heart failure, and angina pectoris will be provided.

### **6.3 Compliance**

Not applicable

## **7. Efficacy Evaluation**

### **7.1 Efficacy Evaluation Indicators**

### **7.2 Methods for Evaluating, Recording, and Analyzing Efficacy Evaluation Indicators**

ePRO and questionnaire data will be collected using electronic devices and stored in the Smart-Pro (tentative name) system on servers contracted by Chubu Electric Power Co., Inc. The data will be displayed on a dedicated web interface to improve patient satisfaction through result viewing during consultations between physicians and patients. Researchers will extract data from the server and manage it as research data. The data will be matched with patient background and medical data, and changes in the utilization of ePRO will be analyzed. Planned analyses include paired t-tests and logistic regression analyses.

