### **2.3 Participant Risk and Benefit**

**Risk:** There is no financial burden. The time required for ePRO and questionnaires is approximately 5 minutes. In the event of adverse events, appropriate medical care will be provided. Participant privacy is respected through linked anonymization. The participant list is password-protected by the information manager, stored on a hard disk, and kept in the Sports Medicine Center office. Specifically, personal information such as the participant's name and medical record number, as well as ePRO and questionnaire results obtained using wearable devices, will be accessed and viewed through the dedicated website for this study. This allows for conversations between physicians and participants regarding trends during consultations, contributing to the improvement of patient satisfaction verified in this study. Researchers can then download and anonymize the data for storage and use within the office's hard disk as anonymized research data.

Only authorized research personnel and maintenance developers of this study system with access rights to website for this trial can register and have access to the personal data of participants. There is no risk of privacy infringement because all downloaded research data undergo anonymization processing.

**Benefits:** The results of ePRO are calculated immediately and visualized on the device, allowing the current scores to be shared between physicians and subjects during consultations. There is no compensation for participation in this study.

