## 4.2 Study method

In this study, participants will be randomly assigned to ePRO monitoring or usual care. We will explain this research face-to-face to the patients and obtain electronic consent. Prior to randomization, patients with HF, AF or CAD will be assigned to KCCQ-12, AFEQT or SAQ respectively. For patients with two or more of these three coexisting cardiovascular diseases, treating physicians will assign an appropriate PRO measure based on their primary cardiovascular disease.

Participants will be randomly assigned to ePRO group or control group. After randomization, they are instructed to respond to the questionnaires for outcome assessment. Patients assigned to ePRO group are also asked to respond to physician assigned PRO measures.

All patients will be followed up on an outpatient basis every 4 weeks ( $\pm 2$  weeks) for a total of 5 visits. At every visit, patients in the ePRO group will receive a smart tablet and answer for the assigned questionnaire (KCCQ-12, AFEQT or SAQ) before entering the examination room. The reports of PROs will be displayed on smart tablets and shared between physicians and patients during medical examination. Patients in the control group received standard care in accordance with the latest clinical guidelines. All patients will be asked to respond to the questionnaires for outcome assessment at the fifth visit

In addition, the following information will be collected from participants through interviews or electronic medical records:

- (1) Patient information: the date of birth, age, sex, height, weight, Vital signs (systolic blood pressure, diastolic blood pressure, heart rate, respiratory rate), family history, past history of illness, medication history.
- (2) Blood tests: White blood cell count (WBC), red blood cell count (RBC), hemoglobin concentration (Hb), hematocrit value (Ht), mean corpuscular volume (MCV), mean corpuscular hemoglobin (MCH), mean corpuscular hemoglobin concentration (MCHC), platelet count (PLT),

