## **4.3 Data**

### **4.3.1 Original data**

Data will be collected from electronic PRO survey, questionnaire for outcome assessment and electronic medical records.

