### **4.3.2 Data Collection**

Data will be collected using electronic devices (e.g. smart tablets) for PRO and questionnaires. These data will be collected five times during consultations (every 4 weeks  $\pm$  2 weeks). Patient background information will be obtained directly from the subjects, and medical information will be gathered from electronic medical records.

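### Protocol Sections 2.3 and 7.2 allow the satisfaction ratings to be shown in the consultation, Section 4.2 shares only PRO reports, and no text shields the primary outcome from the treating physician

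*Combined protocol and SAP*

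**What the plan says.** Protocol Section 4.3.1 names three data sources and keeps two kinds of patient answer apart: "Data will be collected from electronic PRO survey, questionnaire for outcome assessment and electronic medical records".

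Section 7.2 keeps the same two kinds together in storage: "ePRO and questionnaire data will be collected using electronic devices and stored in the Smart-Pro (tentative name) system". Its next sentence adds: "The data will be displayed on a dedicated web interface to improve patient satisfaction through result viewing during consultations between physicians and patients". Section 2.3 says that "ePRO and questionnaire results obtained using wearable devices, will be accessed and viewed through the dedicated website for this study", and gives the purpose: "This allows for conversations between physicians and participants regarding trends during consultations, contributing to the improvement of patient satisfaction verified in this study". Section 4.3.2, on PRO and questionnaire data together, says: "These data will be collected five times during consultations".

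Section 4.2, repeated in SAP Section 3, is narrower. What is shared is described as follows: "The reports of PROs will be displayed on smart tablets and shared between physicians and patients during medical examination". Only the ePRO group is described as completing a disease-specific measure, and it does so before going in to see the physician. Controls receive standard care. Both arms answer the outcome questionnaires after randomization and at the fifth visit.

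The primary endpoint is patient satisfaction on a Likert scale (Protocol 4.1, SAP 1.1). It is compared between arms as mean change from baseline by unpaired t-test (SAP 6.1). The trial is open label (Protocol 4.4).

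**The concern.** The trial has one primary endpoint, a self-rated satisfaction score, and no blinding. If the treating physician can see that score, some patients may answer with the physician in mind. Sections 2.3 and 7.2 also give raising satisfaction as a purpose of the display. If the displayed material includes the satisfaction rating itself, measuring the outcome becomes part of the intervention, and a difference between arms would be hard to attribute to visualizing health status.

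The protocol gives two descriptions of what is displayed and has no rule that protects the outcome answers under either. A site team could follow Section 7.2 to the letter and show satisfaction scores in the consulting room.

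**Working it through.** **The two descriptions side by side**

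| Question | Protocol 2.3, 4.3.2, 7.2 | Protocol 4.2 and SAP 3 |
|---|---|---|
| What is displayed? | ePRO and questionnaire data (2.3, 7.2) | PRO reports |
| In which arm? | No limit stated | PRO measure described for the ePRO group only |
| Where are answers given? | In or at the consultations (4.3.2) | PRO measure before the examination room; place and order not stated for outcome questionnaires |
| How often are outcome questionnaires answered? | Five times (4.3.2) | After randomization and at visit 5 |

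**Does the questionnaire data include satisfaction?** Section 7.2 names ePRO and questionnaire data as two things, and Section 4.3.1 names the second as the outcome instrument. Section 9.5 confirms that the cloud system collects survey responses as well as ePRO. On the plain reading, satisfaction is included.

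**Is there a safeguard elsewhere?** Section 2.3 restricts website access to authorized research personnel and system maintainers. It does not exclude treating physicians, who must use the display for the intervention to work. No other section withholds outcome answers from them.

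**When does visibility bias the comparison?** Let v be the mean shift in the rating caused by visibility, by arm (E, C) and time (baseline 0, visit 5). The bias in the difference of mean changes is

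(v_E5 − v_E0) − (v_C5 − v_C0).

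This is zero if the shifts are the same in both arms, or constant over time within each arm. It is non-zero if the shift develops differently by arm. A ceiling on the Likert scale is a separate route: ratings pushed to the top leave less room for a true difference to appear.

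**Illustration.** The documents give no effect size, SD or power calculation, so there is no figure to reproduce.

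- From the SAP: 25 per arm (1.5), two-sided 5% (2.4), unpaired t-test on change (6.1).
- Assumed: no true effect; a net differential shift d favouring ePRO, in SDs of the change score; complete data.
- SD of change = SD of score × √(2(1 − ρ)). At an assumed ρ = 0.5 the factor is √1 = 1, so the two units coincide. A higher ρ makes the same shift on the score larger in change-score units.
- Degrees of freedom = 2 × 25 − 2 = 48. Noncentrality = d × √(25/2) = 3.536d. Rejection rate = P(|T| > t with 0.975 and 48 df) under the noncentral t.

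| Assumed shift d | Noncentrality | Two-sided rejection |
|---|---|---|
| 0 | 0 | 5.0% |
| 0.1 | 0.354 | 6.4% |
| 0.2 | 0.707 | 10.7% |
| 0.3 | 1.061 | 18.0% |

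**The case against.** The strongest reply is that Section 4.2, repeated in the SAP, is the operative description of method, and that it shares only PRO reports. The Benefits text in Section 2.3 likewise mentions only ePRO results. The protocol also uses the word questionnaire for KCCQ-12, AFEQT and SAQ (Sections 4.2 and 12.1), and conversation about trends fits an instrument answered at every visit better than one answered twice. All of this stands as evidence that the looser wording may be unintended. It does not remove the conflict, because Section 7.2 names both data types before saying that the data are displayed. Section 2.1.3 moreover describes ePRO as covering satisfaction, so the narrow reading does not wholly settle the matter.

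Three stronger readings are tempting, and the documents do not support them.

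- A reader might infer that control patients' answers are displayed, so that controls receive part of the intervention. No section says so; this would follow only from the missing arm limit. No section has controls complete a disease-specific PRO, so at most their outcome answers could be seen, and that is not the visualization of health status under test.
- A reader might infer that patients rate satisfaction in front of the physician. The phrase in Section 4.3.2 is followed by the visit interval and can simply mean at the visits.
- A reader might infer that patients are rating their own physician. The object of the satisfaction rating is not stated, and the strength of any courtesy effect depends on it.

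It is also fair that an equal shift in both arms cancels apart from ceiling effects, and that this is an open-label pilot without a power calculation. Neither is a reason to leave the outcome answers unprotected when protection is cheap.

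**Conclusion.** The point holds as a conflict in the text combined with a missing safeguard. Followed as written, Sections 2.3 and 7.2 permit the treating physician to see the primary outcome ratings, without limit by arm. Section 4.2 and SAP Section 3 describe something narrower, and nothing in either document shields the answers. This rests on reading questionnaire data as including the outcome questionnaire, which Section 4.3.1 supports but usage elsewhere leaves open.

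Whether bias would follow, how large it would be and in which direction cannot be derived from the documents. A differential shift towards ePRO would inflate the apparent effect; a ceiling would hide one. The rates of about 6%, 11% and 18% apply only to the assumed shifts and are not estimates for this trial.

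**What to change.** Reconcile Protocol Sections 2.3, 4.3.2 and 7.2 with Section 4.2 and SAP Section 3 by stating that:

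- only the KCCQ-12, AFEQT or SAQ report is displayed, and only in the ePRO arm;
- outcome questionnaire answers of both arms (satisfaction, PSQ, QoI, well-being, shared decision-making) cannot be viewed by treating staff during the trial;
- both arms complete these questionnaires outside the examination room, at the same point relative to the visit-5 consultation;
- patients are told that their physician will not see these answers.

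Section 4.3.2 should also say which instruments are answered at all five visits and which only after randomization and at visit 5.

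The cost is an access-rights setting in Smart-Pro and a few sentences of text. Sample size and analysis are unchanged. The one small downside is that physicians cannot act on a low satisfaction score while the trial is running.

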### **9.2 Analysis of Results**

Analyses will be performed using multivariate analysis, unpaired t-tests, etc.

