### **1.3. Exploratory endpoint**

Factors associated with improved patient satisfaction in ePRO group

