## **6. Efficacy Analysis**

### **6.1. Primary endpoint**

Patient satisfaction calculated by Likert-Scale. Patient satisfaction, assessed using a Likert scale were compared between the two groups. Mean changes from baseline to the final follow-up were analyzed using unpaired t-tests.

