### **6.2. Secondary endpoint**

1. Assessment of well-being, patient preferences for shared decision-making using questionnaires.
2. Qualitative assessment of ePRO monitoring in ePRO group.

The changes in Patient Satisfaction Questionnaire (PSQ) score and Quality of Information (QoI) related to treatment and prognosis were compared between the two groups. Mean changes from baseline to the final follow-up were analyzed using unpaired t-tests.

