### **6.3. Exploratory endpoint**

Factors associated with improved patient satisfaction in ePRO group

For qualitative data, the changes from before to after the intervention were compared.

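### Protocol 7.2 names paired t-tests where protocol 9.2 and the SAP use unpaired between-arm tests, and the before-after comparison in SAP 6.3 cannot identify factors linked to improved satisfaction

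*Combined protocol and SAP*

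**What the plan says.** **Efficacy tests**

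- Protocol 7.2, within the efficacy evaluation section: "Planned analyses include paired t-tests and logistic regression analyses". No endpoint, arm or time point is attached. The sentence before it says that "changes in the utilization of ePRO will be analyzed".
- Protocol 9.2: "Analyses will be performed using multivariate analysis, unpaired t-tests, etc". Paired tests are not mentioned.
- SAP 6.1 sets the primary comparison, satisfaction "assessed using a Likert scale were compared between the two groups", and names the test: "Mean changes from baseline to the final follow-up were analyzed using unpaired t-tests".
- SAP 6.2 treats the secondary questionnaire scores (PSQ and QoI) in the same way; their changes, "related to treatment and prognosis were compared between the two groups", are again tested with unpaired t-tests. SAP 2.7 repeats the unpaired test for complete data.

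**Exploratory endpoint**

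- SAP 1.3, repeated in SAP 6.3 and protocol 4.1: "Factors associated with improved patient satisfaction in ePRO group".
- The only analysis that SAP 6.3 gives for it: "For qualitative data, the changes from before to after the intervention were compared".

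The SAP text contains neither a paired t-test nor a logistic regression.

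**The concern.** The objective in protocol 2.1.2 and SAP 1 is whether ePRO monitoring improves satisfaction. In a randomised two-arm trial that is a between-arm question. A paired t-test answers a different one: whether scores in one set of patients moved over time. They may move for reasons unrelated to ePRO, such as repeated visits, ongoing standard treatment, regression to the mean, or the expectations that come with an open-label design and a subjective outcome. Because 7.2 lists paired tests for efficacy without saying what they serve, a reader of the results could not tell whether a reported paired p-value was a planned efficacy analysis or a departure from the SAP. SAP 2.5 makes no multiplicity adjustment, so such p-values would also be uncontrolled.

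The exploratory endpoint has a separate problem. It asks which factors go with improvement, and comparing qualitative data before and after the intervention describes change only. SAP 6.3 does not define improvement and gives no list of factors and no model.

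**Working it through.** **1. The passages side by side**

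| Place | Test named | Comparison stated |
|---|---|---|
| Protocol 7.2 | paired t-test, logistic regression | none |
| Protocol 9.2 | multivariate analysis, unpaired t-test | none |
| SAP 2.7 | unpaired t-test | none (complete data) |
| SAP 6.1 | unpaired t-test on change | between the two groups |
| SAP 6.2 | unpaired t-test on change | between the two groups |
| SAP 6.3 | no test named | before v after, qualitative data |

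Protocol 7.2 is the outlier on the t-test.

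**2. What the choice of test does**

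The plan gives no power, effect size or SD, so it has no power figure to reproduce. Its one sample-size figure is consistent: 25 × 2 = 50 (SAP 1.5).

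Inputs: 25 per arm (SAP 1.5); two-sided 5% (SAP 2.4). Assumptions that are not in the documents: no dropout, normal change scores, and the same true change d in both arms (in SDs of the change score), so that ePRO has no effect.

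- Paired test in one arm: df = 25 − 1 = 24, noncentrality = d√25 = 5d.
- Unpaired test on change: df = 50 − 2 = 48, noncentrality = (difference in d)·√(25/2) = 0, so it rejects 5% of the time whatever d is.

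| Common change d | 5d | P(paired p<0.05, ePRO arm) | P(unpaired p<0.05) |
|---|---|---|---|
| 0.2 | 1.0 | 16% | 5% |
| 0.3 | 1.5 | 30% | 5% |
| 0.5 | 2.5 | 67% | 5% |
| 0.8 | 4.0 | 97% | 5% |

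The paired test reaches 80% power at a within-arm change of about 0.58 SD. The unpaired test needs a between-arm difference of about 0.81 SD. The paired test is therefore the easier of the two to pass, and it is the one that does not address the objective.

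**3. SAP 6.3**

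To identify a factor, an analysis must relate that factor to satisfaction across patients. The stated comparison relates time to a qualitative response. The logistic regression in 7.2 may have been meant for this endpoint, but no passage says so. If it were run in the ePRO arm with half the patients improved (assumed), there would be about 25 × 0.5 ≈ 12 events, so dichotomising leaves little to work with.

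Precision of a continuous alternative, assuming a balanced binary factor and expressed in residual SDs of the visit-5 score:

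- Within the ePRO arm (12.5 per level): SE = √(2/12.5) = 0.40; 95% CI about ±1.96 × 0.40 = ±0.8.
- Arm-by-factor interaction in all 50 (12.5 per cell): SE = √(4/12.5) = 0.57; 95% CI about ±1.96 × 0.57 = ±1.1; detectable with 80% power at about (1.96 + 0.84) × 0.57 = 1.6.

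**The case against.** The best defence is that the SAP settles the matter. SAP 6.1 names the endpoint, the comparison and the test. The sentence in 7.2 is an open list, its nearest stated object is ePRO utilisation and not satisfaction, and the multivariate analysis in 9.2 could cover the logistic regression. The trial is a pilot. A within-arm look at factors is also a legitimate, if limited, exploratory question.

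Most of this stands, and it limits the severity. It does not remove the inconsistency. Section 7.2 is the protocol's section on analysing efficacy indicators, and it omits the between-arm test altogether. Protocol 9.6 promises that departures from the analysis plan will be explained, which requires knowing which tests were planned.

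Several stronger readings are tempting, but the documents do not support them:

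- *The control group is discarded.* It is not: SAP 6.1 and 6.2 compare both arms.
- *The paired tests are confined to the ePRO arm.* Section 7.2 names no arm.
- *SAP 6.3 conflicts with the primary test.* It is a separate exploratory endpoint, set in the ePRO group by its own definition.
- *The trial will claim benefit because ePRO is significant and control is not.* With equal change in both arms and power w for each paired test, that pattern has probability w(1 − w). It is at most 0.50 × 0.50 = 25%, reached at a common change of about 0.41 SD. The arithmetic is right, but no passage plans to compare two within-arm p-values.

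**Conclusion.** Two limited defects hold. First, protocol 7.2 names paired t-tests for efficacy and so disagrees with protocol 9.2 and SAP 2.7, 6.1 and 6.2; a paired within-arm result cannot show an effect of ePRO. With no effect and a common change of 0.2 to 0.8 SD, such a test in the ePRO arm would be significant 16% to 97% of the time, against 5% for the planned between-arm test. Those changes are assumed, and the figures show only why the one test cannot stand in for the other. Second, the analysis in SAP 6.3 cannot answer its own endpoint; this follows from the text and needs no assumption.

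Severity is low to moderate. The primary test is identifiable from the SAP, no stated figure changes, and nothing here invalidates the primary comparison.

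**What to change.** - **Protocol 7.2:** delete paired t-tests, or state that within-arm change will be described without a p-value. Tie the logistic regression to a named exploratory use or delete it.
- **Protocol 7.2 and 9.2:** name the same between-arm analysis of change in satisfaction as SAP 6.1, and say that efficacy conclusions rest on it.
- **SAP 6.3:** replace the before-after comparison with a regression of continuous visit-5 satisfaction on one or two pre-listed factors already collected (for example index disease or age), adjusted for baseline satisfaction. The adjustment matters because a factor that merely marks low baseline scores would otherwise appear to predict improvement. Report estimates with 95% CIs, labelled exploratory. If the analysis stays within the ePRO arm, say that it shows association only and not who benefits from ePRO.
- **Optional:** an arm-by-factor interaction in all randomised patients. This changes the exploratory question, so protocol 4.1 and SAP 1.3 would need rewording too, and at n=50 it would be very imprecise.

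The cost is minor rewording in the two protocol sections and SAP 6.3, and a little programming; no new data are needed. The downside is that the exploratory estimates will be imprecise and must be presented that way.
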